### 5.7.3 ADDITIONAL RULES

- **All changes in TAC dose (including all non-study visits) must be performed according to the study protocol and the current TAC trough level target.**
- **TAC adaptations have to be made within 48 hours after the receipt of the TTV load.**
- **The lowest TAC trough level target is 3.5 ng/mL, the highest is 10 ng/mL.**
- **The treating physician can request additional TAC trough levels at any time (also on non-study visits) but TTV load will only be assessed and TAC trough level target changes only performed at the study visits.**
- **If non-adherence is suspected, no increase in TAC trough level target will be performed:** E.g. a failure of TAC intake more than once per week on average for b.d. and once every two weeks on average for o.d. formulation detected by the patient diary. In this case the patient should be educated about medical adherence (e.g. psychological counseling) and the target TAC trough level will not be changed according to TTV load until the next study visit.

### 5.7.4 HINTS FOR INDIVIDUALIZATION OF TAC DOSAGE

**One TAC trough level adaption step is defined as 2 ng/mL (investigators are allowed to target a range of +/- 1 ng/mL; thus one step might be within a minimum of 1 ng/mL and a maximum of 3 ng/mL).** This allows for additional individualization and accounts for limited granularity of TAC dosage formulation. **Additional individualization might be necessary in the following clinical scenarios:**

- **Absolute changes in TAC dose might have different effect sizes on the TTV load.** A change >20% in TAC dose is expected to show significant changes in the TTV load. Thus the upper range of 3 ng/mL might be targeted in case of high TAC intake and the lower range of 1 ng/mL in case of low TAC intake.
- **Significant changes in TTV load are expected 6 weeks (= 1 visit) after a significant change in immunosuppression has been performed. However, the full effect might take up to 12 weeks (= 2 visits).** If a change in the TAC target has been performed at the visit before and another TAC change in the same direction is suggested at the current visit, the lower TAC step range of 1 ng/mL might be targeted.
- **Simultaneous relevant changes in immunosuppression other than TAC might influence the subsequent TTV load** and the risk of infection/rejection. E.g. if mycophenolic acid has to be stopped and the TTV load indicates a TAC decrease, a TAC target change of 1 ng/mL might be performed.
- **The peak TTV level is at month 3 to 4 post-transplantation; thereafter the TTV load shows a gentle decline towards month 12 post-transplantation.** If the TTV load indicates a reduction in the TAC target at Visit 1, but the TAC level is within the local centre range, a TAC target reduction of 1 ng/mL might be performed.

### 5.7.5 ENDPOINT RELATED TREATMENTS

**If subjects experience rejection as defined by the primary end point, severe infection (life or organ threatening defined by investigator (e.g. need for ventilator assistance in CMV pneumonia; but not acute renal impairment during UTI) or relevant BK infection (e.g. presumptive PVAN defined by  $\geq 10^4$  c/mL BKV [or corresponding U/mL] in the plasma detected by PCR or biopsy proven PVAN), the investigator may decide for participants of the active group to continue TTV-guided TAC dosing or to stopped and to continue using the protocol of the control arm (see stopping rules).**

**If the investigator decides to continue, the following rules apply:**

• **Rejection:**

- if TTV load suggests TAC trough level target step down, this suggestion must not be followed and TAC trough level target will be chosen by the investigator (e.g. stay on TAC trough level target or increase TAC trough level target)
- if TTV load suggests no change in TAC trough level target this suggestion may be followed or TAC trough level target may be chosen by the investigator (e.g. increase TAC trough level target)

• **Severe infection:**

- If TTV load suggests TAC trough level target step up, this suggestion must not be followed and TAC trough level target will be chosen by the investigator (e.g. stay on TAC trough level target or decrease TAC trough level target)
- If TTV load suggests no change in TAC trough level target this suggestion may be followed or TAC trough level target may be chosen by the investigator (e.g. decrease TAC trough level target)

• **Relevant BKV infection:**

- If a TAC trough level target step down is indicated by TTV load, a 'reduction of TAC as a treatment response to BKV' is the preferred strategy.
- If no TAC trough level target change is indicated by TTV load, a 'reduction of the antimetabolite as a treatment response to BKV' is the preferred strategy.
- If a TAC trough level target step up is indicated by TTV load, it has to be ignored and a 'reduction of the antimetabolite as a treatment response to BKV' is the preferred strategy.
- Investigators are encouraged not to use a 'switch from mycophenolic acid to azathioprine' as treatment response for BKV.
- Introduction of IVIG is possible independently of the treatment strategy and the TTV load.

### 5.7.6 CONTROL GROUP

**TAC will be dosed according to TAC trough target levels defined by the local centre standard.** TAC will be quantified at every study visit. Additional TAC quantification may be ordered by the treating physician at any time.

The TTV load will be accessed but not revealed to the investigator. TTV results must not be entered in the hospital data system used for routine care but have to be entered in the eCRF by the personnel, who performed the TTV assessment. TTV results in the eCRF will only be visible for the treating clinical personnel in the active/interventional group.

### 5.7.7 GENERAL RULE

- **No change in TAC** dosing should be performed **if the TAC** trough level **does not reflect a steady state** e.g. due to:
  - Low TAC level due to a missed dose or earlier intake than usual the day before the blood draw.
  - High TAC level due to an intake at the morning before the blood was drawn or later than usual at the day before the blood draw.
  - Suspected drug or dietary interaction with TAC.
  - Suspected high TAC levels due to diarrhea.

In these cases, the TAC trough level has to be repeated within a week. If TAC level is back to a steady state, TAC dosing has to be performed according to the allocated treatment group.

- **Corticosteroids and antimetabolites will not be dosed according to the TTV level.**  
Centres are encouraged to keep the antimetabolite dose stable.

## 5.8 EMERGENCY MEASURES

In the event of a serious adverse reaction (possibly due to the trial drug dosing) or an emergency, subjects have the opportunity to contact the trial site or to introduce themselves personally. After clinical assessment, the appropriate emergency measures are initiated there. In the event of a dosing related problem, a temporary dose adaption or stop of the trial shall be applied in accordance with chapter 5.7 and 6.21. In the event of emergency treatment outside of the trial site, the subject shall present the trial card. Unblinding is not necessary due to the study design (investigator not blinded to allocation).

## 5.9 CONCOMITANT MEDICATION

Subjects are not allowed to receive cyclosporine, mTor inhibitor or co-stimulation blocker (Belatacept) based immunosuppression or significant additional long term (e.g. weeks) immunosuppression (e.g. cyclophosphamide) or immune modulation (e.g. check-point inhibitors). This does not include therapy for organ rejection, PVAN or TMA. In addition, herbal preparations containing St. John's Wort (*Hypericum perforatum*) or other herbal preparations should be avoided when taking TAC due to the risk of interactions that lead to decrease in blood concentrations of tacrolimus and reduced clinical effect of tacrolimus.

## 5.10 ADHERENCE

Medical adherence will be monitored prospectively by patient diary. Non-adherence is defined as failure of TAC intake more than once per week on average for b.d. and once every two weeks for o.d. formulation. If missing entries of medical intake in the patient diary suggests non-adherence, the trial personnel has to verify if this is due to true non-compliance or due to inaccurate completion of the patient diary. Additional electronic drug monitoring using MEMS® Buttons (AARDEX Group, Switzerland) on TAC blisters, the BAASIS questionnaire, claimed prescriptions, psychological evaluation and TAC trough level variability will be accessed retrospectively.

## 5.11 BLINDING AND EMERGENCY ENVELOPES

### 5.11.1 BLINDING

The study will be conducted using a single-blind design (participants blinded). Assessors of the primary outcome will also be blinded to allocation: all episodes of infection and allograft rejection will be assessed by personnel blinded to the randomization code (infection: two infectious disease specialists; rejection: two kidney pathologist; Vienna based). The randomization code will be kept with the sponsor. No clinical staff member has access to the treatment randomization codes. Unblinding is not necessary due to the study design (investigator not blinded to allocation).

### 5.11.2 EMERGENCY ENVELOPES

Unblinding is not necessary due to the study design (investigator not blinded to allocation).

### 5.11.3 PREMATURE UNBLINDING IN AN EMERGENCY

Unblinding is not necessary due to the study design (investigator not blinded to allocation).

### 5.11.4 REGULAR UNBLINDING

Regular unblinding for the assessors and patients is performed after the end of the clinical trial and data evaluation (closing of the database).

## 6 COURSE OF THE CLINICAL TRIAL

### 6.1 IMPLEMENTATION OF INFORMED CONSENT

Potential study patients will be informed about the trial (aims, methods, implications, benefits and risks of the trial, voluntary nature of participation, right to refuse participation, samples and data collection and procedures for unexpected events) in terms they can fully understand, and written informed consent will be obtained prior to inclusion.

As a general starting point, patients are entitled to:

- understand that participation is voluntary.
- ask questions and receive understandable answers before making a decision.
- know the degree of risk and burden involved in participation.
- know who will benefit from participation.
- know the procedures that will be implemented in the case of incidental findings.
- receive assurances that appropriate insurance coverage is in place.
- know how their biological samples and data will be collected and protected during the trial and either destroyed or reused at the end of the trial.
- know of any potential commercial exploitation of the research.

All consent forms will be signed following the general rule that in the prior information-giving session, the patients concerned were given written and verbal information on the study by an investigator. At the end of the session, they are specifically asked whether they have understood all the relevant aspects of the study described and whether they are aware of their rights and duties as study participants. The patient is not asked to sign the consent form until he/she confirms that he/she has no further questions and wants to voluntarily participate in the study and to adhere to the protocol and the required long-term follow-up. The patient concerned can choose to do so directly after the information-giving session or later, after an appropriate period for reflection. The consent documentation will be in the original languages of the patients to be recruited for the study. When submitting the application for review by the competent local/national ethical boards/bodies for authorization, detailed information will be provided on the informed consent procedures that will be implemented. Copies of examples of informed consent forms and information materials will be included. These will be in language and terms understandable to the participants.

The informed consent materials will include, inter alia, the following data:

- a statement that the study involves research subjects;
- an explanation of the purpose of the research and the expected duration of the subject's participation;
- a description of the procedures to be followed and identification of any procedures that are experimental;
- a description of any reasonably foreseeable risks or discomforts to the subject;
- a description of any benefits to the subject or to others that may reasonably be expected from the research;
- a disclosure of appropriate alternative procedures or courses of treatment that might be advantageous to the subject;
- a statement describing the extent, if any, to which confidentiality of records identifying the subject will be maintained;

- for research involving more than minimal risk, an explanation of whether there are any treatments or compensation if injury occurs and, if so, what they consist of, or where further information may be obtained;
- an explanation of whom to contact for answers to pertinent questions about the research and research subjects' rights, and whom to contact in the event of a research-related injury to the subject;
- a statement that participation is voluntary, that refusal to participate will involve no penalty or loss of benefits to which the subject is otherwise entitled and that the subject may discontinue participation at any time without penalty or loss of benefits to which the subject is otherwise entitled.

In order to maintain data subject privacy, data will be identified by study number only. The investigator will keep a separate log of subject names and addresses in a secure place. However, in compliance with Good Clinical Practice, the study monitor may review the part of the subject's medical record that is directly related to the study. Prior to implementation, any amendments to the protocol that have subject safety implications must be approved by the appropriate IRBs and other competent regulatory authorities. Measures that are critical for subject safety may be implemented simultaneously with appropriate and timely reporting to the relevant IRBs and the competent regulatory authorities.

#### Incidental findings:

In principle, patients have the right to decide whether they are informed about incidental findings or not. The majority of the examinations are routine clinical practice and would also be performed independently of the study. Therefore, information about the handling of incidental findings must be provided in accordance with the prevailing clinical standard. No incidental findings are expected as a result of the TTV test. The central reporting (pathology and infection) is only used for endpoint recording and is not communicated back to the centers and patients, thus incidental findings do not exist. For these reasons, explicit study-specific information on incidental findings is not necessary.

All subjects have the right to withdraw at any time during the study without prejudice and this will be communicated clearly and often. There will be continuous safety and efficacy follow-up for each subject. The following circumstances constitute signs for withdrawal of the patient, and participating researchers will be alert to these contexts:

- withdrawal of consent by the patient/legal representative;
- any clinical condition that, in the investigator's opinion, could constitute a risk to the patient and that would prevent the appropriate conduct of the trial; and
- loss of capacity to consent.

## 6.2 REGISTRATION/RANDOMIZATION

Participants will be allocated at a ratio of 1:1 using random permuted blocks with variable block size, stratified by recruiting centre. Eligible patients will be randomized 1:1 to either

- Torque Teno virus-guided immunosuppression (arm T) or
- Standard dosing (arm S).

eCRF-based randomisation will be used. Patients will be registered at screening.

Randomization occur at visit 1 (post-transplant month 4) after confirming the inclusion/exclusion criteria. Randomization list will be created via the program nQuery-Advisor® and included in the eCRF. Implementation according to the allocation sequence will be performed by the trial personnel.

Randomization will be conducted only if the patient can be included in the study (checking of inclusion- and exclusion criteria, written consent of the patient).

### 6.3 SCREENING V-3 (AT THE WARD IN THE FIRST WEEK POST-TRANSPLANTATION; LATEST UNTIL DISCHARGE)

Screening is the process of determining whether a person is suitable for inclusion in a clinical trial. For this purpose, the following information is recorded or examinations are carried out after the consent of the trial subject has been obtained (see 6.1):

#### **Required information:**

- Information and written informed consent of the subject,
- Preliminary inclusion / exclusion criteria check

#### **Required investigations:**

- Laboratory workup (TTV R-GENE®)
- Biobanking

### 6.4 SCREENING V-2 AND V-1 (AT ROUTINE VISIT IN MONTH 2 AND 3 POST-TRANSPLANTATION)

#### **Required investigations:**

- Laboratory workup (TTV R-GENE®; TAC-trough level; chemistry; CBC; urine analysis)
- Biobanking

### 6.5 VISIT 1 (DAY 0; AFTER DAY 93 POST-TRANSPLANTATION, WITHIN MONTH 4 POST-TRANSPLANTATION)

After the final assessment of the inclusion and exclusion criteria, the subject is admitted to the trial and randomized if suitable (see 6.2).

The following information is recorded or investigations are performed:

#### **Required information:**

- Inclusion/Exclusion criteria
- Medical history
- Medication
- Vital signs
- Physical examination, body weight
- Pregnancy test

#### **Required investigation:**

- Laboratory workup (TTV R-GENE®; TAC-trough level; chemistry; CBC; vBGA; urine analysis; BKV and CMV; DSA)
- Biobanking
- Quality of life (SF-36; MTSOSD-59R)
- Drug adherence (MEMS® BUTTON; patient diary; BAASIS, psychological evaluation)
- Data sampling concerning protocol biopsy performed according to local centre standard; protocol biopsy has to be performed before V1

**Required Intervention:**

- Adaption of TAC dose

**6.6 VISIT 2 (WEEK 6; ± 14 DAYS)****Required information:**

- Vital signs
- Medication
- Adverse events
- Primary endpoint

**Required investigation:**

- Laboratory workup (TTV R-GENE®; TAC-trough level; chemistry, CBC, vBGA; urine analysis; BKV and CMV)
- Biobanking
- Drug adherence (MEMS® BUTTON; BAASIS; patient diary)

**Required Intervention:**

- Adaption of TAC dose

**6.7 VISIT 3 (WEEK 12; ± 14 DAYS)**

Like Visit 2

**6.8 VISIT 4 (WEEK 18 ± 14 DAYS)**

Like Visit 2

**6.9 VISIT 5 (WEEK 24; ± 14 DAYS)**

Like Visit 2.

**6.10 VISIT 6 (WEEK 30; ± 14 DAYS)**

Like Visit 2.

**6.11 VISIT 7 (FINAL VISIT: WEEK 36 ± 14 DAYS)****Required information:**

- Vital signs
- Physical examination, body weight
- Pregnancy test
- Medication
- Adverse events
- Primary endpoint

#### **Required investigation:**

- Laboratory workup (TTV R-GENE®; TAC-trough level; chemistry, CBC; vBGA; urine analysis; BKV and CMV; DSA)
- Biobanking
- Drug adherence (MEMS® BUTTON; BAASIS; patient diary; claimed prescription check, psychological evaluation)
- Quality of life (SF-36; MTSOSD-59R)
- Data sampling concerning protocol biopsy performed according to local centre standard

### 6.12 FOLLOW-UP

The final adaption on TAC range will be performed on visit 6. FUP will last for 6 weeks until visit 7 (last visit).

### 6.13 ROUTINE CALLS

Routine calls every two weeks will help to detect infections treated outside the study centre.

### 6.14 DEVIATIONS FROM THE PROTOCOL

The principal investigator is responsible for ensuring that the clinical trial is conducted at the trial site in accordance with the trial protocol. If there are nevertheless deviations from the valid protocol, specified procedures, GCP and/ or the applicable regulatory requirement(s), these must be documented by the trial site, including a clear description and justification.

Subject-related deviations are documented in the eCRF. Subject-independent deviations are documented on a separate form, which is stored in the ISF.

Deviations from the protocol are e.g.:

|                                                                             | minor | major | critical |
|-----------------------------------------------------------------------------|-------|-------|----------|
| Deviations in relation to the inclusion or exclusion criteria               |       |       | X        |
| Examinations/visits that were missed                                        |       | X     |          |
| Examinations/visits that did not take place within the given time window    | X     |       |          |
| Non-performance of laboratory analyses in regard to TTV-level determination |       | X     |          |
| Non-Adherence in regard to IMP intake                                       |       | X     |          |
| Incorrect administration of the IMP (dosing)                                |       | X     |          |
| Intake of expired IMP                                                       |       | X     |          |

|                                                                                |  |   |   |
|--------------------------------------------------------------------------------|--|---|---|
| Excluded concomitant medication has been taken by the patient                  |  | X |   |
| Treatment not as randomized                                                    |  |   | X |
| Incorrect adjustment of the IMP according to TTV-level in the TTV guided group |  | X |   |
| Deviations that have led to an (S)AE                                           |  | X |   |

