## 6.16 ASSESSMENT OF SAFETY

### 6.16.1 SPECIFICATION OF SAFETY PARAMETERS

- Death
- Graft loss
- Infection and rejection according to the primary and secondary endpoints
- Acute kidney injury (>grade I according to the Acute Kidney Injury Network)
- New onset of diabetes mellitus (according to the American Diabetes Association)
- Fluid overload (>5% increase in body weight)
- Hypercholesterolemia (LDL >160mg/dl) and hypertriglyceridemia (>150mg/dl)
- Arterial hypertension (>140/90 mm Hg)
- Cardiovascular event (myocardial infarction, unstable angina, stroke, peripheral artery disease >grade III, hospitalisation due to cardiac decompensation)
- Prolongation of the QTc interval (>500 ms) and Torsade de Pointes tachycardia
- Hyperkalaemia (>6 mmol/L)
- Nausea, vomiting, diarrhoea, constipation
- Posterior reversible encephalopathy syndrome, delirium, seizure and coma, tremors, paraesthesia, headache, mental status change, and changes in motor and sensory function, insomnia, asthenia and pain
- Anaemia (Hb<6mg/dl)
- Malignoma

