### *Infection*

**All infections have to be documented as adverse events.**

**In general quality, onset and duration of symptoms, details on diagnostic, treatment in-patient stay, and response to treatment have to be noted.**

**Signs of infections which have to be documented as an adverse event include** pain, night sweat, fever, chills, malaise, fatigue, diarrhea (frequency and consistency of the stool) abdominal pain/cramps, dysuria, pollakisuria, alguria, urinary urgency/frequency, suprapubic pain, flank/allograft pain (on palpitation), caught, sputum (purulent, with blood), adventitious breath sounds on auscultation/palpation, shortness of breath, and rapid/shallow breathing.

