## 10.3 STATISTICAL ANALYSIS

### 10.3.1 DEFINITION OF EVALUTION POPULATIONS

The primary analysis will be performed on a modified intention to treat (mITT) principle. Sensitivity analyses will be performed according to intention to treat and per protocol (PP) analysis, and the dataset restricted to adherent patients. Further sensitivity analyses are described below.

Different analysis sets are defined as follow:

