#### **PP set**

This analysis set comprises all subjects who received study intervention and did not critically or majorly violate the protocol in a way that might affect the evaluation of the effect on the primary objective. A list of potential protocol deviations is given in section 6.14.

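### Per-protocol exclusion can depend on the outcome, because one class of major deviation is defined by having led to an adverse event

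*Protocol*

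**What the plan says.** Section 10.3.1 sets the roles of the populations: "The primary analysis will be performed on a modified intention to treat (mITT) principle". ITT, PP and adherent-set analyses are sensitivity analyses.

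The PP set keeps subjects who received the intervention and "did not critically or majorly violate the protocol in a way that might affect the evaluation of the effect on the primary objective". For the deviations concerned it adds: "A list of potential protocol deviations is given in section 6.14".

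Section 6.14 holds a table of example deviations graded minor, major or critical. One row, graded major, is "Deviations that have led to an (S)AE". The row "Examinations/visits that did not take place within the given time window" is graded minor. Missed examinations or visits are graded major, with no reference to when they occur.

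Section 6.17, under Infection, states: "All infections have to be documented as adverse events". Section 3.2 makes infection the first component of the primary composite, provided it required inpatient treatment, antimicrobial drugs or reduced immunosuppression. Section 6.16.1 lists as safety parameters death, graft loss and "Infection and rejection according to the primary and secondary endpoints".

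**The concern.** Ten of the eleven rows in the 6.14 table describe what was done or not done. The remaining row describes what happened afterwards. Once such a row feeds the PP definition, two patients with the same deviation can be handled differently because of their outcome. If both attend a visit outside its window, and one visit is judged to have led to an infection, that patient's deviation becomes major while the other's stays minor. The missed-visit row raises a related problem, because a visit missed on account of an endpoint event also counts as major.

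The purpose of a PP analysis in a non-inferiority trial is to show whether departures from the protocol have blurred a real difference. If membership depends partly on the endpoint, agreement between PP and mITT is weaker evidence than it appears, and disagreement is harder to interpret.

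**Working it through.** **Step 1: follow the text.**

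- Section 10.3.1 removes major and critical violators from the PP set and points to 6.14 for the deviations.
- Section 6.14 makes a deviation major if it led to an AE or SAE, whatever its nature.
- Section 6.17 makes every infection an AE, and section 3.2 makes most treated infections primary endpoint events (SARS-CoV-2 is excluded).
- The limiting clause in 10.3.1 asks whether the violation might affect evaluation of the primary objective. A deviation judged to have caused an endpoint event meets that test easily, so the clause does not screen these cases out.

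**Step 2: see how much the row adds.** The table has ten other rows. Nine are already major or critical whatever follows, and only the out-of-window row is minor. The consequence-defined row therefore adds exclusions only for out-of-window visits, or for minor deviations not in the table, that are judged to have led to an event.

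**Step 3: reproduce the plan's own figure.** Section 10.2 gives 120 per arm, expected rates 0.30 (arm T, TTV-guided) and 0.40 (arm S, standard), a margin of 0.10 and one-sided alpha of 2.5%.

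- SE = √(0.30×0.70/120 + 0.40×0.60/120) = √0.00375 = 0.06124
- Power = Φ((0.10 − (0.30 − 0.40))/0.06124 − 1.960) = Φ(3.266 − 1.960) = 90.42%

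This matches the stated power. Nothing in this point changes it.

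**Step 4: illustrate the effect on the PP difference.** Let f be the share of patients with a primary endpoint event who are removed through this row. The documents give no value, so f is an assumption, varied from 0 to 20% per arm. Of N patients with event rate p, N·p·f are removed, and the PP event rate becomes

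p′ = p(1 − f)/(1 − p·f), with N(1 − p·f) patients left.

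Take 130 per arm and true rates of 50% (T) and 40% (S), so that the true difference lies exactly at the margin. These rates are illustrative; the plan expects 30% and 40%. For f = 10% in arm T only:

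- p′ = 0.50×0.90/(1 − 0.05) = 0.45/0.95 = 0.4737, with 130×0.95 = 123.5 patients left
- PP difference = 0.4737 − 0.40 = 7.4 points
- SE = √(0.4737×0.5263/123.5 + 0.40×0.60/130) = 0.0622
- Chance of meeting the margin in the PP analysis = Φ((0.10 − 0.0737)/0.0622 − 1.960) = 6.2%

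The same formulas give:

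| f in T | f in S | PP rate T | PP rate S | PP difference | Chance of meeting the margin |
|---|---|---|---|---|---|
| 0 | 0 | 50.0% | 40.0% | 10.0 points | 2.5% |
| 5% | 0 | 48.7% | 40.0% | 8.7 | 4.0% |
| 10% | 0 | 47.4% | 40.0% | 7.4 | 6.2% |
| 20% | 0 | 44.4% | 40.0% | 4.4 | 14.1% |
| 10% | 5% | 47.4% | 38.8% | 8.6 | 4.1% |
| 20% | 10% | 44.4% | 37.5% | 6.9 | 7.0% |
| 5% | 5% | 48.7% | 38.8% | 9.9 | 2.6% |
| 10% | 10% | 47.4% | 37.5% | 9.9 | 2.6% |
| 20% | 20% | 44.4% | 34.8% | 9.7 | 2.8% |
| 0 | 5% | 50.0% | 38.8% | 11.2 | 1.5% |
| 0 | 10% | 50.0% | 37.5% | 12.5 | 0.9% |
| 0 | 20% | 50.0% | 34.8% | 15.2 | 0.3% |

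For scale, f = 5% in arm T is 130×0.50×0.05 = 3.25 patients, and f = 20% is 13. The imbalance between arms drives the shift; equal removal leaves the difference almost unchanged.

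**The case against.** The strongest reply is that 6.14 is a GCP classification of examples and not an exclusion list. Section 10.3.1 calls its entries potential deviations and adds the limiting clause on the primary objective. That is fair as far as it goes, but 6.14 is the only source 10.3.1 names, and the clause does not remove the cases at issue (Step 1).

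Several other objections stand and limit the point:

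- A reader might infer that patients leave the PP set simply for having the primary endpoint. The text does not say so. A deviation is needed, together with a judgement that it led to the event and relevance to the primary objective. An infection alone removes nobody.
- A reader might infer that unblinded site staff make that judgement. Section 6.14 has the site document and justify deviations, and sections 5.8 and 5.11.1 say that investigators know the allocation. No section says who grades deviations or decides what led to what.
- A reader might add that the row "Incorrect adjustment of the IMP according to TTV-level in the TTV guided group" tilts the PP set because only the TTV-guided arm can breach it. That is a weak argument. The row does not depend on outcome, and the table also has general rows for incorrect dosing and for treatment not as randomised, which can capture departures in the control arm.
- Blinded finalisation of the PP list before database lock is ordinary SAP content. Its absence from the protocol is not a fault.

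**Conclusion.** Wrong as written, for a sensitivity analysis only. The protocol lets PP membership depend on the primary outcome through a deviation class defined by its consequence.

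The number of patients affected is probably small, because nine of the ten other rows already count as major or critical. It is tempting to conclude that the rule biases the PP result towards non-inferiority. The documents do not support a direction. That bias arises only if removals fall mainly in the TTV-guided arm; balanced removal is close to neutral, and removal mainly from the standard arm works against non-inferiority. All sizes above rest on assumed shares removed and illustrative true rates at the margin.

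The mITT primary conclusion, the sample size and the 90.42% power do not change. Nor does the protocol make the non-inferiority conclusion conditional on the PP result. What suffers is the value of the PP analysis as corroboration.

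**What to change.** Amend the PP definition in section 10.3.1 in three respects:

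1. State that, for the PP set, deviations are classified by their nature and not by their consequence.
2. Take the consequence-defined row out of the PP criteria. Keep it in 6.14 for GCP and safety reporting.
3. State that deviations arising after or because of the first primary endpoint event, such as a visit missed on account of it, do not count towards PP exclusion.

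The cost is a wording change in 10.3.1, carried into the SAP. No extra data collection, patients or change to the primary analysis is needed. Deviations and endpoint events must be dated to apply the third item; the time-to-first-event analysis in 10.3.3 already needs event dates.
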